#### **8.1.8 Blinding**

This is an open-label study.

## **9. STUDY PROCEDURES AND ASSESSMENTS**

### **9.1 Study Flow and Visit Schedule**

The study-specific assessments and procedures are shown in Table 2.

**Table 2. Study Assessments and Procedures Schedule**

|                                                                       | Screening
day-30 | Baseline
Day -30
to Day
-1 | Rhenium-
SCT
treatment
Day 0 | post
treatment
within 14
days | Monthly
post 14 day
follow up
visit for 12
months-Via
App | 30-day post
treatment
phone call | 3
month
follow
up | 6
month
follow
up | 12
month
follow
up/ end
of study
visit | 24
months           |
|-----------------------------------------------------------------------|---------------------|-------------------------------------|---------------------------------------|----------------------------------------|--------------------------------------------------------------------------|----------------------------------------|----------------------------|----------------------------|-------------------------------------------------------|------------------------|
| Permissible day range                                          |                     |                                     |                                       | +/-48
hours                 | +/-48
hours                                                   | +/-5 days                       | +/-4
days       | +/-4
days       | +/-7
days                                  | +/- 14
days |
| Inclusion/ exclusion criteria                                  | X                   |                                     |                                       |                                        |                                                                          |                                        |                            |                            |                                                       |                        |
| Urine pregnancy test                                           |                     |                                     | X                                     |                                        |                                                                          |                                        |                            |                            |                                                       |                        |
| Histology****                                                  | X                   |                                     |                                       |                                        |                                                                          |                                        |                            |                            |                                                       |                        |
| Informed consent                                               | X                   |                                     |                                       |                                        |                                                                          |                                        |                            |                            |                                                       |                        |
| Demographics                                                   |                     | X                                   |                                       |                                        |                                                                          |                                        |                            |                            |                                                       |                        |
| Medical history                                                |                     | X                                   |                                       |                                        |                                                                          |                                        |                            |                            |                                                       |                        |
| Concomitant medications                                        |                     | X                                   | X                                     | X                                      |                                                                          |                                        | X                          | X                          |                                                       |                        |
| Photos via App*                                                |                     |                                     |                                       |                                        | X                                                                        |                                        |                            |                            |                                                       |                        |
| Photography at site follow up visits (site camera)             |                     | X                                   |                                       | X                                      |                                                                          |                                        | X                          | X                          | X                                                     | X                      |
| CTCAE grading/wound assessment                                 |                     |                                     |                                       | X                                      |                                                                          |                                        | X                          | X                          | X                                                     | X                      |
| QoL questionnaire* via App                                     |                     | X                                   |                                       |                                        |                                                                          |                                        |                            | X                          | X                                                     |                        |
| Comfort of treatment* via App                                  |                     |                                     |                                       | X                                      |                                                                          |                                        |                            |                            |                                                       |                        |
| Treatment with Rhenium-SCT                                     |                     |                                     | X                                     |                                        |                                                                          |                                        |                            |                            |                                                       |                        |
| Cosmetic outcome - Subject rated* via App                      |                     |                                     |                                       |                                        |                                                                          |                                        |                            |                            | X                                                     | X                      |
| Cosmetic outcome - Clinician rated                             |                     |                                     |                                       |                                        |                                                                          |                                        |                            |                            | X                                                     | X                      |
| AEs***                                                         |                     |                                     | X                                     | X                                      |                                                                          | X                                      |                            |                            |                                                       |                        |
| MODIFIED VISUAL RECIST**                                       |                     | X                                   |                                       |                                        |                                                                          |                                        |                            | X                          | X                                                     | X                      |
| Histology if lesion visible/suspected/or per clinical practice |                     |                                     |                                       |                                        |                                                                          |                                        |                            |                            | X                                                     | X                      |

|                                                            |  |  |  |  |  |  |  |  |  |   |
|------------------------------------------------------------|--|--|--|--|--|--|--|--|--|---|
| Review for wound complications or radiation changes |  |  |  |  |  |  |  |  |  | X |
|------------------------------------------------------------|--|--|--|--|--|--|--|--|--|---|

\*QoL, subject rated cosmetic outcome, monthly photos obtained through subject trial App; \*\* baseline visual RECIST is to measure lesions only; \*\*\* AE's to be recorded for the first 30 days post treatment. After this only treatment related AEs are to be recorded: \*\*\*\* Histology must be confirmed to meet the inclusion criteria before any baseline assessments are conducted

AE: Adverse events; QoL: Quality of life; RECIST: Response evaluation criteria in solid tumours

NOTE: In case of early termination: In case of premature termination during the follow-up period, the investigator shall endeavour to arrange a premature end of study visit and perform examinations according to end of treatment visit. If the subject does not enter the follow-up period, this is the study termination (end of study) visit.

NOTE: Radiation changes at months 24 are to be recorded as the CTCAE grading in protocol appendix 1, excluding Radiation dermatitis.

NOTE: Subjects who do not have a smart phone will complete QoL questionnaire, Comfort of treatment questionnaire and Cosmetic outcome on paper questionnaires at the follow up visits. Monthly photos are not taken for subjects without a smart phone, instead photos are taken at the site, at follow-up visits only.

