**Safety endpoint:**

- Adverse events by severity and by relationship to Rhenium-SCT, including radiation dermatitis, dry skin, skin ulceration, alopecia, skin induration, hypo/hyperpigmentation, and telangiectasia.

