**Safety**

Common Terminology Criteria for Adverse Events (CTCAE) 5.0 grading for acute and late effects, relevant to treatment:

- Radiation dermatitis
- Skin ulceration
- Alopecia
- Skin induration
- Hypo/hyperpigmentation

- Telangiectasia

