### **5.5 Safety Endpoint**

- Safety: Adverse events (AEs) by severity and by relationship to Rhenium-SCT, including radiation dermatitis, skin ulceration, alopecia, skin induration, hypo/hyperpigmentation, and telangiectasia.

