### **9.1.1 Informed Consent Visit / Screening and baseline (Day -30 to Day -1)**

The subject will be fully informed of all study procedures and implications both verbally and in writing via use of an informed consent form. Once a subject has signed the informed consent form, a subject number (identifier) will be assigned.

Within 30 days prior to the administration of the first dose of study medication, the following procedures and assessments must be completed, and all inclusion and exclusion criteria must be met.

- Obtain informed consent
- Check of inclusion and exclusion criteria, including confirmation of BCC or SCC via histology AND confirmed by clinician review
- Target lesion(s) dimensions including depth of lesion
- Demographic data
- Baseline Modified Visual RECIST (dimensions only)
- QoL Questionnaire (via App or via eCRF or paper for subjects with no phone)
- Medical history
- Relevant concomitant medication
- Photographs of lesions to be treated are taken at the site and uploaded to the eCRF (if a medical photographer is available this is preferable)

The investigator will review all information obtained from the screening procedures. Screening failures, i.e., screened subjects not in compliance with all criteria, are to be excluded and the reason will be recorded. Subjects who fulfil all the inclusion criteria and none of the exclusion criteria will be eligible to participate in the study. Information of subject's study participation can be provided to the subject's general practitioner upon request, provided the subject has given consent for this to occur and this consent is documented in the source notes accordingly.

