## 10. PHARMACOVIGILANCE

### 10.1 Definition of Adverse Events

An AE is defined as any untoward medical occurrence in a subject administered a treatment and which does not necessarily have a causal relationship with this treatment. An AE can therefore be any new sign, symptom, illness, or syndrome, any abnormal laboratory values, if judged clinically significant in the opinion of the investigator, any worsening (change in nature, severity or frequency) of a concomitant or pre-existing illness, any adverse effect of the investigational medicinal product/device, including comparator or concomitant medication, any product/device interactions, any adverse effect of an invasive procedure required by the protocol or any accident or injury, whether or not related to the investigational medicinal product/device.

All AEs fall into one of two categories: “non-serious” and “serious”.

In this study, the following medical events will not be considered to fall under the definition of an AE:

- Surgical procedures or other therapeutic interventions themselves are not AEs, but the condition for which the surgery/intervention is required is an AE and should be documented accordingly.
- Planned surgical measures and the condition(s) leading to these measures are not AEs, if the condition(s) was (were) known before the period of observation and did not worsen during study. In the latter case, the condition should be reported as medical history.
- Any SAEs detected by the investigator in a study subject after the end of the period of observation, which the investigator does not consider to be related to prior study treatment or procedures

Progression of the cancer under study is not considered an AE unless it results in hospitalization or death.

The study will collect all AEs for the first 30 days of the study, after which only AE's deemed treatment (device) related will be collected.

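### The Appendix 1 skin terms are never graded before treatment, so separating pre-existing skin changes from device effects rests on photographs, medical history and investigator judgement

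*Protocol*

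**What the plan says.** Section 5.5 of the protocol defines the safety endpoint as "Adverse events (AEs) by severity and by relationship to Rhenium-SCT, including radiation dermatitis, skin ulceration, alopecia, skin induration, hypo/hyperpigmentation, and telangiectasia". The synopsis, under criteria for evaluation, describes the tool as "Common Terminology Criteria for Adverse Events (CTCAE) 5.0 grading for acute and late effects, relevant to treatment". Appendix 1 gives the grade definitions.

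Table 2 schedules "CTCAE grading/wound assessment" at the 14-day visit and at 3, 6, 12 and 24 months. A note to the table and the 24-month visit list in 9.1.3 exclude radiation dermatitis from the 24-month grading.

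Before treatment, 9.1.1 asks for "Baseline Modified Visual RECIST (dimensions only"), and a footnote to Table 2 repeats that "baseline visual RECIST is to measure lesions only". The same list includes medical history and photography: "Photographs of lesions to be treated are taken at the site and uploaded to the eCRF".

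Section 10.1 counts as an adverse event, among other things, "any new sign, symptom, illness, or syndrome", a worsening of a pre-existing illness, and any adverse effect of the device. Sections 9.1.2.3, 10.1, 10.4 and 10.5 restrict collection after day 30 to events judged related to treatment.

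The synopsis safety endpoint has a slightly different list of terms: "including radiation dermatitis, dry skin, skin ulceration, alopecia, skin induration", followed by the pigmentation changes and telangiectasia.

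**The concern.** With no control arm, the state of the site before treatment is the only internal reference for local skin effects. The listed signs are not specific to radiation and may already be present at a tumour site or on sun-damaged skin around it. Appendix 6 itself expects scabs over the tumour that must be removed before treatment.

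After day 30 the judgement of origin decides more than the label on an event. It decides whether the event enters the adverse event data at all, and 10.4 leaves exclusion of a device association beyond that day to the investigator's discretion. Late effects are graded out to 24 months, so most scheduled gradings fall in this period. An error could go either way: existing signs may be charged to the device, or true late effects may be set aside as already present. A statistical analysis plan cannot repair this, because it cannot supply a baseline value that was never collected.

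**Working it through.** No power, error rate or stated figure enters this point. The check is a reading of the schedule against the adverse event rules, plus one area calculation that bears on the fix.

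**1. Scheduled gradings.** Table 2 has ten columns. The CTCAE row has marks in five: day 14 and months 3, 6, 12 and 24. The three pre-treatment or treatment columns (Screening, Baseline, Day 0) have none.

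- Radiation dermatitis: 5 − 1 (month 24 excluded) = 4 gradings after treatment, 0 before.
- Ulceration, alopecia, induration, hypo- and hyperpigmentation, telangiectasia: 5 after, 0 before.

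**2. What is recorded before treatment.** Section 9.1.1 lists lesion dimensions and depth, medical history, relevant concomitant medication, demographics, quality of life and site photographs. Section 9.3 adds Fitzpatrick skin type and defines medical history as relevant conditions and illnesses. None of these is a structured record of the Appendix 1 signs at the site.

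**3. How far photographs go.** Site photographs are taken at baseline and at all five follow-up site visits, so a visual comparison exists. It has two limits.

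- The baseline instruction covers the lesions. It does not say that the 5 mm margin, which 8.1.1 includes in the marked area, must be in the picture.
- Appendix 1 grades induration by whether the skin can be slid or pinched, about which a photograph says little.

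**4. What a grade could add for pigmentation and telangiectasia.** For these terms Appendix 1 places the border between Grades 1 and 2 at 10% of body surface area. Inputs: lesion area up to 8 cm² (7.1, item 7), margin 5 mm (8.1.1), up to three target lesions (7.1, item 3). Assumptions: circular lesions and a body surface of 1.5 to 2.2 m².

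- Lesion radius = √(8/π) = 1.60 cm; with margin 2.10 cm.
- Treated area = π × 2.10² ≈ 14 cm² per lesion, about 41 cm² for three.
- 10% of body surface = 1,500 to 2,200 cm².

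On area alone, a treated site stays in Grade 1 however much it changes. A baseline grade by itself would show a new sign (absent to Grade 1) but not local worsening of an existing one. For these terms, presence or absence and the photograph must be used as well.

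**5. Dry skin.** It is named in the synopsis safety endpoint. It is absent from the synopsis CTCAE list, from 5.5 and from Appendix 1.

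**The case against.** The strongest reply is that the protocol does not leave sites without a reference. Photographs are taken before treatment and at each follow-up site visit, medical history covers past and present conditions, and 10.5.4 requires other causes to be weighed when relatedness is assigned. This stands. A reader might infer that existing changes cannot be separated from radiation effects at all. The documents do not support that: separation is possible in part, but it is unstructured and weakest for induration.

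A reader might also infer that 10.1 makes a pre-treatment grade a condition for calling something an adverse event. It does not. The definition also covers any adverse effect of the device, and it describes worsening as a change in nature, severity or frequency, which photographs and history can support.

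Eligibility narrows the problem further. Section 7.2 excludes prior surgery, radiation or laser at the target site, and lupus, scleroderma, xeroderma, vitiligo and albinism. Sun damage and signs of the tumour itself remain.

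Finally, the skin terms are introduced as examples within a wider endpoint of all adverse events, so they should not be read as the whole of it. Dry skin reported as an adverse event would still be graded under 10.5.2; only the dedicated list omits it. Both points stand.

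**Conclusion.** The point holds as a modest design weakness. No structured pre-treatment grade of the Appendix 1 terms is scheduled, so a named part of the safety endpoint lacks a graded reference, in a single-arm, open-label study where relatedness governs recording after day 30. Attribution rests on photographs, history and judgement. The primary endpoint, sample size and error rates are not touched.

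The size of the bias, and its direction, cannot be derived from the documents. A reader might try to size it by assuming that 10% to 40% of sites already show a sign and that new signs arise independently in 10%. Then 1 − (1 − 0.10)(1 − 0.10) = 19% and 1 − (1 − 0.40)(1 − 0.10) = 46% would show a sign later. Those figures are not evidence. Both inputs are invented, the formula assumes that every baseline sign persists although signs belonging to the tumour may go with it, and it yields a prevalence, whereas the endpoint is adverse events by severity and relationship.

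The dry-skin mismatch is a separate, minor inconsistency.

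**What to change.** - In Table 2, add a mark to the CTCAE row in the Baseline column, or on Day 0 before treatment, and a matching line in 9.1.1. Record the presence or absence and the Appendix 1 grade of each term at each target site, including the 5 mm margin.
- Require the baseline photograph to cover the same area.
- Report skin effects after treatment as new or worsened against that record. For pigmentation and telangiectasia, use presence or absence and the photograph as well as the grade.
- Reconcile dry skin: either include it in 5.5, the synopsis CTCAE list and Appendix 1, or remove it from the synopsis safety endpoint.

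The cost is one more eCRF page and a few minutes per subject. If done at Baseline, the lesion is already being measured and photographed at that visit. No new visit, staff or invasive procedure is needed. Subjects already treated would have no baseline grade; their baseline photographs can give partial support and they should be identified as such in the report.

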### **9.1.2.3 Day 30 Phone call**

On day 30, post treatment, the site will call the subject as this forms the end of the AE reported period. After this time, only AEs deemed related to treatment will be collected. During the call any AEs are to be recorded into the eCRF.

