### **9.1.3 Follow-up**

Each month following the 14-day site follow-up visit, subjects who have a smart phone will be prompted via the trial App to take 2 photos of each lesion treated (one is taken in indoor light and one in natural light).

Site Follow up visits will occur at 14 days, 3 months, 6 months, 12 months and then 24 months.

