#### **12 month follow up visit:**

- Photography of treated lesions (medical photographer or site digital camera)
- CTCAE grading
- Quality of Life questionnaire completed via trial App (or on paper during the visit if subject does not have a smart phone)
- Cosmetic outcome; subject rated. To be completed on Trial app (or directly into the eCRF if the subject does not have a smart phone). VAS image found in the protocol appendix 3
- Cosmetic outcome: Clinician rated. To be completed into the eCRF using VAS in the protocol appendix 3
- Modified Visual RECIST assessment. Guide to assessment is found in protocol appendix 5
- Histology to be performed if lesion is visible, suspected or if this is the site's regular clinical practice

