**24 month follow up visit:**

- Photography of treated lesions (medical photographer or site digital camera)
  - CTCAE grading. Grading can be found in protocol appendix 1
  - Cosmetic outcome; subject rated. To be completed on Trial app (or directly into the eCRF if subject does not have a smart phone). VAS image found in the protocol appendix 3
  - Cosmetic outcome: Clinician rated. To be completed into the eCRF using VAS in the protocol appendix 3
  - Modified Visual RECIST assessment. Guide to assessment is found in protocol appendix 5
- 
- Histology to be performed if lesion is visible, suspected or is the site's regular clinical practice
  - General review for wound complications and radiation changes. Radiation changes at months 24 are to be recorded as the CTCAE grading in protocol appendix 1, **excluding** Radiation dermatitis.

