## 10.4 Period of Observation

All AEs that occur after the consent form is signed but before treatment with investigational medicinal products/devices must be reported by the investigator if they cause the subject to be excluded from the study or are the result of a protocol-specified intervention.

For the purposes of this study, the period of observation for collection of AEs extends from the time when the subject signed informed consent until 30 days after the treatment administration.

If the Investigator detects a SAE in a study subject after the end of the period of observation (i.e., 30 days post treatment to 24 months) and considers the event related to prior study treatment or procedures, he or she should contact the Medical Monitor to determine how the AE should be documented and reported. An SAE form should be completed and sent to Medical Monitor.

Association of an event with the device can be excluded (at investigator discretion if deemed unrelated to treatment) if the event occurs later than the following latency period after the last product/device application:

- 30 days for non-serious adverse events,
- 30 days for SAEs
- 30 days for pregnancy, or 30 days if the subject initiates new anticancer therapy, whichever is earlier

If events occur after these latency periods, they will not be recorded, unless deemed associated (related) with the device treatment.

Any SAE brought to the attention of an investigator at any time outside of the time period specified above must be reported immediately to the Sponsor if the event is considered to be product/device related.

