## 10.5 Documentation and Reporting of Adverse Events

Adverse events, SAEs, and other reportable safety events will be reported by the participant (or, when appropriate, by a caregiver, surrogate, or the participant's legally authorized representative).

The investigator, who is a qualified physician, and any designees are responsible for detecting, assessing, documenting, and reporting events that meet the definition of an AE or SAE as well as other reportable safety events. Investigators remain responsible for following up AE, SAEs and other reportable safety events for outcome.

All AEs (whether serious or non-serious) for the first 30 of the study must be documented in the eCRF. After 30 days, only AE's and SAE's deemed treatment associated will be collected.

The Investigator must document all AEs that occur during the first 30 days of the study on the respective pages provided in the eCRF in accordance with the instructions for the completion

of adverse event reports in clinical studies. These instructions are provided in the Investigator file and in the eCRF itself.

Every attempt should be made to describe all AEs in terms of a diagnosis. If a clear diagnosis has been made, individual signs and symptoms should not be recorded unless they represent atypical or extreme manifestations of the diagnosis, in which case they should be reported as separate events. If a clear diagnosis cannot be established, each sign and symptom must be recorded individually.

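### Table 2 and Section 9.1.3 disagree on when adverse events are asked about, and neither schedules an adverse event item at months 12 or 24 although treatment-related events are to be recorded after Day 30.

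*Protocol*

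**What the plan says.** **The collection rule.** All AEs are recorded for 30 days and treatment-related AEs after that. The Table 2 footnote says "AE's to be recorded for the first 30 days post treatment. After this only treatment related AEs are to be recorded". Section 9.1.2.3, on the Day 30 call, says "After this time, only AEs deemed related to treatment will be collected". Section 10.5 says "After 30 days, only AE's and SAE's deemed treatment associated will be collected". Section 10.1 repeats the rule, and Section 10.4 has later events recorded if they are judged device-related. None of these places gives an end date for non-serious related events. For related serious events, Section 10.4 names the window "30 days post treatment to 24 months". Under Section 6.1, subjects stay in the study for 24 months after treatment.

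**The schedule.** Section 9.1.3 states "Site Follow up visits will occur at 14 days, 3 months, 6 months, 12 months and then 24 months". The AE row of Table 2 is marked at Day 0, the 14-day visit and the 30-day call, and is blank at all later visits. The visit lists in Section 9.1.3 include AEs at months 3 and 6 but not at months 12 or 24.

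**Other safety items at the later visits.** Table 2 marks CTCAE grading and wound assessment at the 14-day visit and at months 3, 6, 12 and 24. The 24-month list adds "General review for wound complications and radiation changes", with radiation dermatitis left out of what is recorded.

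**What the data feed.** The safety endpoint (synopsis and Section 5.5) is AEs by severity and by relationship to the device. Section 11.8.1.1 summarises coded AEs in the same way.

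**The concern.** Section 6.1 sends sites to the Section 9 schedule for visit details, and Section 9.1 points to Table 2. A site working from Table 2 finds no AE item after Day 30, while a site working from the Section 9.1.3 lists asks at months 3 and 6. Sites could therefore follow the same protocol and solicit events differently, and neither schedule carries out the collection rule at months 12 and 24.

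This matters because the safety endpoint is built on AEs. The synopsis says CTCAE grading is meant to capture both acute and late effects, and late effects of a single radiation treatment arise in the part of follow-up where the AE item is absent. An event that is neither a graded skin term nor visible at the treated site enters the AE data only if the subject volunteers it or the investigator asks unprompted. A later analysis plan cannot recover events that were never asked about.

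**Working it through.** No sample size, power or error rate is involved. The check sets the schedules beside the collection rule and counts the gap.

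**Step 1. The four site visits after Day 30.**

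| Visit | AE item in Table 2 | AE item in 9.1.3 | CTCAE grading and wound assessment in Table 2 | Treatment-related AEs to be recorded under the rule |
|---|---|---|---|---|
| Month 3 | No | Yes | Yes | Yes |
| Month 6 | No | Yes | Yes | Yes |
| Month 12 | No | No | Yes | Yes |
| Month 24 | No | No | Yes, plus a general wound and radiation review; radiation dermatitis not recorded | Yes |

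The entries in the last column are explicit to 24 months for related serious events (Section 10.4). For non-serious related events they follow from a rule with no end date combined with 24 months of participation (Section 6.1).

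**Step 2. Count.**

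- Table 2: the last AE item is at Day 30. Visits without an AE item: 4 of 4. Time after the last item: about 24 − 1 = 23 of 24 months, and 23/24 ≈ 96%.
- Section 9.1.3: the last AE item is at month 6. Visits without an AE item: 2 of 4. Time after the last item: 24 − 6 = 18 of 24 months, and 18/24 = 75%.

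These percentages are shares of calendar time after the last item labelled as AEs. They do not estimate the share of events lost.

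**Step 3. What the other items cover.** Appendix 1 grades seven terms: radiation dermatitis, skin ulceration, alopecia, skin induration, hypopigmentation, hyperpigmentation and telangiectasia. Without radiation dermatitis, six remain at month 24. Wound assessment adds what can be seen at the treated site.

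**Step 4. What is left without a prompt.**

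- Pain and other non-visible related events: neither a graded term nor a visible finding.
- Dry skin: named in the synopsis safety endpoint, but absent from Section 5.5 and not listed as a term in Appendix 1. Dry desquamation appears there only within grade 1 radiation dermatitis, the term that drops out at month 24.

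These have no scheduled AE prompt at months 12 and 24, nor at months 3 and 6 if a site follows Table 2.

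**The case against.** The strongest reply is that late safety is actively assessed. CTCAE grading and wound assessment are scheduled at all four later visits, and the graded terms are those named in the Section 5.5 endpoint. Treated lesions are photographed at each of these visits. Smartphone users also send monthly photographs for 12 months, which the investigator or study nurse looks at. Cosmetic outcome is rated by subject and clinician at months 12 and 24. Scarring and infection would usually be visible, and bleeding is part of the higher radiation dermatitis grades until that term is dropped at month 24. The duty to record related events stands in the footnote to the AE row itself. Section 10.5 makes investigators responsible for detecting events, and Sections 10.4 and 10.6 require related serious events to be reported whenever they come to attention. The AE completion instructions sit in the investigator file and the eCRF, which are not shown.

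Most of this stands, and it limits the point. A reader might infer that late related events are missed, or that follow-up has no safety enquiry for 75% or 96% of its length. The documents do not support either reading: such events are unsolicited by a labelled item, and other safety assessments continue. Nor do they support reading the 24-month window as an explicit requirement for every related event, because that sentence in Section 10.4 concerns serious events.

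What the reply does not remove is the conflict between Table 2 and Section 9.1.3 at months 3 and 6, the absence of an AE item from both at months 12 and 24, and the lack of a prompt for events that are neither graded nor visible.

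**Conclusion.** The point holds as an internal inconsistency with a bounded consequence. The two schedules contradict each other at months 3 and 6, and both fall short of the protocol's own collection rule at months 12 and 24. The size is two of four later site visits without an AE item under Section 9.1.3, and four of four under Table 2. The exposed events are related ones outside the Appendix 1 terms and visible wound findings, with pain and dry skin as examples.

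The conclusion assumes that sites take their visit procedures from Section 9 and that nothing in the unseen eCRF instructions supplies the missing prompt. It also takes the open-ended rule for non-serious related events to run through the 24 months of participation. A reader might go further and infer that the safety endpoint will look better than the truth. Under-recording is possible, but the documents give no basis for its size or for asserting that it will occur. The correction should be made, because it is cheap and protects the stated safety endpoint.

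**What to change.** Reconcile Table 2, Section 9.1.3 and Section 10:

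- In Table 2, mark AEs at months 3, 6, 12 and 24, labelled as treatment-related only after Day 30.
- In Section 9.1.3, add an AE item to the 12- and 24-month visit lists, and apply the same label to the items at months 3 and 6.

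This applies the existing rule and does not widen what is collected. The cost is amended schedule wording, handled under Section 14.3, and one additional question at visits that already take place.
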